### Secondary end points

1. Number of participants failing treatment

2. Incremental cost-effectiveness and cost utility of adalimumab added to MTX compared with MTX alone

3. Health status according to the multiattribute Health Utility Index Mark 2

4. Safety, tolerability and compliance, defined as follows:

a. Adverse events (AEs) and serious adverse events (SAEs)

b. Laboratory parameters (haematological and biochemical analysis and urinalysis)

c. Development of human antihuman antibody to adalimumab determined with samples collected at 1, 6 and 18 months

d. Participant diaries and dosing records will determine tolerability and compliance throughout the trial treatment period

5. Use of corticosteroids over the duration of the study period and throughout follow-up, including the following:

a. Total oral corticosteroid dose

b. Reduction and reduction rate of systemic corticosteroid dose from entry dose

c. Topical corticosteroid use (frequency) compared to use at time of entry

d. Need for pulsed corticosteroid

6. Optic and ocular outcomes, defined as follows:

a. Number of participants with disease flares (defined by worsening based on SUN criteria) following a minimum of 3 months of disease control

b. Number of participants with disease flares within the first 3 months of the study

c. Visual acuity as measured by age-appropriate logMAR assessment

d. Number of participants with resolution of associated optic nerve or macular oedema (as assessed by slit-lamp biomicroscopy or OCT (where available)

e. Number of participants with disease control (defined as zero cells with topical treatment for 3 and 6 months)

f. Number of participants entering disease remission (defined as zero cells without topical treatment for 3 and 6 months)

g. Duration of sustaining inactive disease (zero cells with or without topical treatment)

7. Quality of life assessments (Childhood Health Questionnaire and Childhood Health Assessment Questionnaire)

8. ACR Pedi core set criteria at ACR30, ACR50, ACR70, ACR90 and ACR100 levels

9. Number of participants with disease flares, in remission on and off medication [53], related to their JIA and with minimum disease activity [54]

10. Number of participants requiring change in biologic and/or disease-modifying antirheumatic drug therapy for arthritis due to failure to respond

### Study population

#### Inclusion criteria

Participants are eligible for the trial based upon having at least one eye fulfilling the following eligibility criteria:

1. Children and young people ages 2 years and older up to and including 18 years of age and fulfilling the International League Against Rheumatism diagnostic criteria for JIA (all subgroups with uveitis)

2. At the time of trial screening, participants must have active anterior uveitis, defined as a sustained grade of cellular infiltrate in anterior chamber of SUN criteria grade ≥1+ or more during the preceding 12 weeks of therapy despite MTX and corticosteroid (both systemic and topical) therapy

3. They must have failed MTX therapy previously (minimum dose of 10 to 20 mg/m^2^ with a maximum dose of 25 mg/participant)

4. Participants must have been on MTX for at least 12 weeks and on a stable dose for 4 weeks prior to the screening visit; omission of a maximum of 2 weeks of MTX treatment within these 12 weeks is acceptable and will not render patients ineligible, unless the omission occurs within the 4 weeks prior to the screening visit

5. No disease-modifying immunosuppressive drugs, other than MTX, in the 4 weeks prior to screening

6. Written informed consent of participants or their parents or legal guardians, as well as assent where appropriate

7. Participants and their parents or legal guardians must be willing and able to comply with protocol requirements

8. For participants of reproductive potential (males and females), use of a reliable means of contraception throughout trial participation; postpubertal females must have a negative serum pregnancy test within ten days before receiving the first dose of the trial drug

9. Ability to be randomised and commence the trial treatment within 2 weeks of the screening visit

21. Intraocular pressure control requiring more than one topical pressure-lowering therapy or requiring systemic acetazolamide

### Selection of centres/clinicians

The study will be initiated at centres once all their global requirements (for example, local research and development (R&D) approval) and study-specific conditions (for example, training requirements) have been met and all necessary documents have been returned to the Medicines for Children Research Network Clinical Trials Unit (MCRN CTU). Initiation meetings will cover the requirements outlined in the Clinical Trials Research Centre’s standard operating procedures related to site training and setup.

### Centre/clinician inclusion criteria

The following are the inclusion criteria for centres and clinicians:

1. Centres offering a combined paediatric rheumatology/ophthalmology service

2. All participants recruited should have regular and emergency access to a paediatric rheumatologist and/or ophthalmologist

3. Completion of calibration training in ophthalmology assessments

4. Sufficient demonstrated capacity of staff to carry out study assessments

5. Curriculum vitae (CV), including a record of International Conference for Harmonisation (ICH) of Good Clinical Practice (GCP) training of the Principal Investigator (PI)

6. CV including a record of ICH GCP training of other personnel on the delegation log

7. Completion and return of the ‘Signature and Delegation Log’ to the CTU

8. Positive site-specific information

9. Local R&D approval

10. Signed contract between site and sponsor

11. Receipt of evidence of completion of criteria 8 to 10 by CTU

12. Ability to perform biochemical assessments

All sites are expected to demonstrate the ability to run paediatric clinical trials in accordance with GCP and as such demonstrate support and infrastructure for all aspects of trial delivery, including integration of the clinical research teams with pharmacy, clinical laboratory and research support services. All centres will be expected to work in collaboration with MCRN CTU support where present, including the National Institute for Health Research MCRN local research networks, the Comprehensive Local Research Network and their equivalents in Scotland, Wales and Northern Ireland.

### Centre and clinician exclusion criteria

Centres and clinicians will be excluded if they do not meet the inclusion criteria and expectations stated above.

### Sample size

The sample size is based on data regarding failure rates from 62 patients on MTX in a comparable population provided by [name] of Great Ormond Street Hospital. After 3 months, 11 patients had disease control based on grade 0 SUN criteria (18%), and therefore, on the basis of the trial inclusion criteria, they would not be eligible for inclusion in the trial. At 15 months following the start of treatment with MTX, 23 patients of the 51 who had failed at 3 months had achieved disease control (45%), leaving 28 (55%) who had not. The null hypothesis underlying this trial is that there is no significant difference between adalimumab and placebo in controlling disease activity of JIA-associated uveitis unresponsive to MTX therapy.

To detect a relative reduction of 50% between a failure rate of 60% and 30% with 90% power, at 5% significance and 2:1 randomisation, a total of 140 patients (93 adalimumab and 47 placebo) are required. There is unlikely to be a trial of this nature again in the near future; therefore, we have increased the power of the study to 90% from the conventional power level of 80% to optimise the detection of a significant difference between treatment regimens if one truly exists. A trial of adalimumab in JIA with or without MTX powered the study using a 40% absolute (57% relative) difference in the rate of flare between the placebo and adalimumab groups [41].

The advent of biological therapies in JIA has led international investigators to a paradigm shift in the treatment of JIA and its related complications, leading to significantly more ambitious outcomes in clinical trials, including elimination of inflammation and normalisation of short-term and long-term function [15,55]. To this end, instead of previously accepted clinical outcomes of 30% absolute difference in JIA patient outcomes between active agent and placebo [56], increasingly significant differences are being expected and regarded as significant, with new definitions of response being established for use in clinical trials, such as clinical remission and minimal disease activity [53,54]. Indeed, 40% of patients in the adalimumab JIA trial were reported as showing an ACR Pedi 100 response (100% response rate) at 2 years [41].

The clinically relevant outcomes of JIA-associated uveitis may take years to develop, and the relationship between isolated measures of clinical activity and long-term outcomes remains ill-defined. Recent studies suggest that the length of continuously controlled activity is likely to be of more clinical relevance than short-term improvements in activity levels.

In view of these factors, as well as the expectation expressed unanimously through consumer consultation in the development of this trial protocol, we have set a minimum 50% relative difference in failure rates between interventions. We estimate that loss to follow-up will be approximately 10% based on (1) the severe nature of the disease potentially resulting in loss of vision, (2) clinical opinion arising from an *a priori* meeting of investigators representing participating centres, (3) feedback from consumer representatives and (4) the exisiting experience of the investigators and consumer representatives with compliance with current use of biologic therapies in JIA-associated uveitis. Therefore, we increased the sample size by approximately 10%, giving us a total of 154 patients (102 adalimumab and 52 placebo).

### Randomisation

Randomisation will be undertaken during normal working hours (Monday to Friday from 0900 to 1700) by the pharmacy departments of participating centres upon receipt of a randomisation request form and prescriptions from authorised clinicians. Pharmacy personnel will verify that these documents are appropriately completed before proceeding. The PI and delegated research staff are responsible for (1) notifying pharmacy personnel of potential randomisations so that they can ensure adequate drug supplies are available on-site and (2) completing the appropriate trial documents and delivering these to the pharmacy department at their centres so that pharmacy personnel can proceed with randomisation.

Participants will be randomised using a secure (24-hour) web-based randomisation programme. Randomisation lists will be generated at a 2:1 ratio in favour of the active therapy. The lists will incorporate random elements, and the web randomisation programme will be controlled centrally by the MCRN CTU. Both measures are being employed to ensure that participant allocations are concealed. Participant treatment allocation will be displayed on a secure website, and an automated email confirmation will be sent to the authorised randomiser. In the event of an internet connection failure between the centre and the randomisation system, the centre should contact the MCRN CTU immediately to try to resolve the problem. If this is not possible within a reasonable amount of time, then the supplied backup randomisation envelopes will be used to provide the treatment allocation.

### Assessments and procedures

After written consent (and assent where appropriate) from the parent or legal guardian or from the trial participant, is obtained, medical and ophthalmic histories will be taken and recorded on the appropriate case report form (CRF) with particular emphasis on other disorders of relevance and allergies. Separate sections on the CRF will be provided to record the JIA and uveitis-specific medical and ophthalmic histories and the participant’s other medical and surgical histories. Medication use (prescriptions, over-the-counter medicines and herbal supplements) during the 4 weeks prior to the screening visit will also be recorded. Information from a physical examination, measures of disease activity and complications, laboratory tests (haematological and biochemical analysis and urinalysis) and medication and surgical histories will be gathered at the screening visit and again at each subsequent trial visit.

Protocol assessments will be performed according to the table of assessments (Table 1).

**Table 1 T1:** **Study visits and assessments**^**a**^

		**Time (months)**															
		**Randomisation and commencement of treatment**								**End of treatment**						**End of trial**	
**Events and assessments**	**Screening**^**b**^	**0**^**c**^	**1**	**2**	**3**	**6**	**9**	**12**	**15**	**18**	**21**	**24**	**27**	**30**	**33**	**36**	**Premature withdrawal**
Written informed consent	X																
Confirmed consent (verbal)		X	X	X	X	X	X	X	X	X	X	X	X	X	X		
Assessment of eligibility criteria	X	X															
Review of medical/ophthalmic/surgical history	X																
Review of concomitant medications	X	X	X	X	X	X	X	X	X	X	X	X	X	X	X	X	X
Pregnancy test (serum)		(X)			X	X	X	X	X	X	X						
Purified protein derivative tuberculin skin test^d^/test for latent TB as locally performed	X																
Urinalysis^e^	X		X	X	X	X	X	X	X	X	X	X	X	X	X	X	X
Randomisation		X															
Study intervention		X	X	X	X	X	X	X	X	X							
Compliance with study intervention		X	X	X	X	X	X	X	X	X							
Physical examination: complete	X		X	X	X	X	X	X	X	X	X	X	X	X	X	X	X
Vital signs (heart and respiratory rates, temperature, blood pressure)	X		X	X	X	X	X	X	X	X	X	X	X	X	X	X	X
Height	X		X	X	X	X	X	X	X	X	X	X	X	X	X	X	X
Weight	X		X	X	X	X	X	X	X	X	X	X	X	X	X	X	X
Childhood Health Questionnaire		X	X	X	X	X	X	X	X	X							
Childhood Health Assessment Questionnaire		X	X	X	X	X	X	X	X	X							
Health Utilities Index Mark 2 questionnaire		X			X	X	X	X		X			X			X	X
Client Service Receipt Inventory		X															
Sample for DNA collection	(X)				(X)					(X)							
RNA and serum/plasma	(X)				(X)					(X)							
Haematological analysis	X		X	X	X	X	X	X	X	X	X	X	X	X	X	X	X
Biochemical analysis	X		X	X	X	X	X	X	X	X	X	X	X	X	X	X	X
Samples for HAHA analyses^f^	X				X												
ANA, dsDNA and ENA	X							X									
Ophthalmic assessments																	
Vision assessment	X		X	X	X	X	X	X	X	X	X	X	X	X	X	X	X
Optical coherence tomography (optional)	(X)		(X)	(X)	(X)	(X)	(X)	(X)	(X)	(X)	(X)	(X)	(X)	(X)	(X)	(X)	(X)
Assessment of vitritis	X		X	X	X	X	X	X	X	X	X	X	X	X	X	X	X
Slit-lamp biomicroscopy	X		X	X	X	X	X	X	X	X	X	X	X	X	X	X	X
Cataract scoring	X		X	X	X	X	X	X	X	X	X	X	X	X	X	X	X
Goldmann tonometry or Tono-Pen	X		X	X	X	X	X	X	X	X	X	X	X	X	X	X	X
Standard ACR paediatric core set outcome variables	X		X	X	X	X	X	X	X	X	X	X	X	X	X	X	X
Tanner score	X				X			X			X	X	X	X	X	X	X
Review of participant diaries	X		X	X	X	X	X	X	X	X	X	X	X	X	X	X	(X)
Assessment of adverse events	X		X	X	X	X	X	X	X	X	X	X	X	X	X	X	X

^a^ACR, American College of Rheumatology; ANA, antinuclear antibody; dsDNA, double-stranded DNA; ENA, extractable nuclear antigen; HAHA, human antiadalimumab antibody to adalimumab; TB, tuberculosis; (X), as applicable/indicated/appropriate. ^b^All procedures should be done before study intervention. ^c^Visit 0 must be completed and treatment must be commenced within 14 days of the screening visit (10 days for pregnancy test). ^d^Participants who are PPD-positive at screening will require a chest X-ray. Treatment of participants who have a positive PPD skin test and/or abnormal chest X-ray should be carried out in accordance with regional and/or national guidelines and initiated at least 4 weeks prior to the first dose of trial medication. Participants with recent (within 6 months of trial entry screen) positive PPD test (≥5 mm) who are being treated with appropriate prophylaxis may request a waiver for a PPD screening from the Medicines for Children Research Network Clinical Trials Unit. Documentation of the positive PPD test should be available, as well as chest X-ray reports, from the date of the positive PPD test and treatment or prophylaxis history from near the time of the participant’s conversion. ^e^Microscopic urinalysis will be obtained at baseline and for other visits only if relevant abnormalities greater than trace are noted on the dipstick analysis. ^f^To be done also as required if anaphylaxis occurs during trial.

With regard to treatment timelines, ‘1-month treatment’ is defined as 4 weeks. After treatment is commenced, the appointments for each subsequent visit should be made for 4 weeks or 3 months (12 weeks) afterwards, depending on the visit schedule. An allowance of −7 days or +7 days will be allowed for monthly visits and −15 days or +15 days for the 3-month visits. Should unscheduled visits be required for any reason, they will be recorded on the ‘unscheduled visit’ CRF. To define treatment failure, there should be an interval of at least 4 weeks between assessments.

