### Known potential benefits

In rheumatoid arthritis phases I to IV studies [50], all individual components of the adult ACR response criteria (number of tender and swollen joints, physician and patient assessment of disease activity and pain, disability index Health Assessment Questionnaire scores and C-reactive protein (mg/dl) levels) improved at 24 or 26 weeks compared to placebo. In these studies, adalimumab-treated patients achieved statistically significant improvement in their rheumatoid arthritis symptoms based on ACR criteria showing 20% improvement (ACR20) and ACR50 responses compared to placebo as early as 1 to 2 weeks after initiation of treatment.

In polyarticular course JIA, adalimumab has been shown to have a significant clinical benefit in improving JIA on the basis of core paediatric ACR response criteria [51]. In the double-blind withdrawal design phase of the trial of adalimumab in JIA patients [41], amongst patients not receiving MTX, there was a significant increase in the number of disease flares in those patients who subsequently received placebo compared to those given adalimumab (71% vs. 43%; *P* = 0.03) [52]. In those patients receiving concomitant MTX, flares occurred in 65% on placebo compared to 37% who received adalimumab (*P* = 0.02). At 48 weeks, the percentage of patients treated with MTX who had ACR Pediatric 30 response criteria (Pedi 30), Pedi 50, Pedi 70 and Pedi 90 responses was significantly greater for those treated with adalimumab than for those given placebo (ACR Pedi 30: 63% vs. 38%, *P* = 0.03; ACR Pedi 50: 63% vs. 38%, *P* = 0.03; ACR Pedi 70: 63% vs. 27%, *P* = 0.002). Open-label extension of the studies showed sustained responses for up to 104 weeks of treatment. As outlined in the protocol rationale, its reported use in JIA-associated uveitis warrants a RCT trial to assess its clinical effectiveness and safety.

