## Methods/design

### Trial design

The SYCAMORE Trial will randomise 154 patients ages 2 to 18 years with active JIA-associated uveitis (despite MTX treatment for at least 12 weeks). All participants will be treated for 18 months, with follow-up of 3 years from randomisation (continuing on MTX throughout). All participants will receive a stable dose of MTX as well as either adalimumab (20 mg/0.8 ml for patients <30 kg or 40 mg/0.8 ml for patients weighing 30 kg or more, subcutaneous injection every 2 weeks based on body weight) or placebo (0.8 ml as appropriate according to body weight) by subcutaneous injection every 2 weeks. Figure 1 shows the schematic of trial design.

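### Table 1 leaves both childhood questionnaires, the only instruments of secondary end point 7, out of the premature-withdrawal visit, and the questionnaire and ACR core-set rows may need reconciling

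*Protocol article*

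**What the plan says.** The section on assessments and procedures in the protocol article makes Table 1 the governing schedule. Four of its rows matter here.

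- "Childhood Health Questionnaire" and "Childhood Health Assessment Questionnaire": marked at month 0 and at each visit up to month 18; blank from month 21 to month 36 and in the premature-withdrawal column.
- "Health Utilities Index Mark 2 questionnaire": marked at months 0, 3, 6, 9, 12, 18, 27 and 36 and at premature withdrawal.
- "Standard ACR paediatric core set outcome variables": marked at screening, at every visit from month 1 to month 36, and at premature withdrawal.

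Vision, vitritis, slit-lamp examination, cataract scoring and tonometry are also marked at premature withdrawal, with optical coherence tomography as applicable.

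Under Secondary end points, item 7 reads "Quality of life assessments (Childhood Health Questionnaire and Childhood Health Assessment Questionnaire" and item 8 reads "ACR Pedi core set criteria at ACR30, ACR50, ACR70, ACR90 and ACR100 levels". Neither carries a time frame. Item 5, on corticosteroid use, does say that it extends over follow-up. Treatment lasts 18 months and follow-up 36 months (Trial design).

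The Analysis plan reports continuous secondary outcomes as differences in means and undertakes to keep missing data to a minimum. It checks the complete case analysis against sensitivity analyses with imputation, and keeps participants who stop treatment but remain in the study under follow-up.

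**The concern.** An exit visit is the last chance to learn how a participant was doing on leaving. Table 1 uses it for nearly every outcome, including another questionnaire, but not for the two instruments that make up end point 7. The article gives no reason. Burden is an unlikely one, since families already complete the Health Utilities Index there.

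If children leave because they are doing badly, and do so more often in one arm, the quality-of-life comparison among those who stay is distorted. The planned imputation analyses would then have no observation at the time of leaving to inform them. Data that were never collected cannot be recovered by a later analysis plan.

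The second issue is whether a site can tell from Table 1 if it should give the Childhood Health Assessment Questionnaire when it records the core set after month 18 or at withdrawal. If that questionnaire supplies a core-set item, the table gives two different answers.

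**Working it through.** The article states no figure for this point that could be reproduced. The check is a column-by-column reading of Table 1, which has 17 visit columns (screening, months 0 to 36, premature withdrawal). Each of the four rows resolves to 17 cells, so no column has slipped in the text.

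| Row | Columns marked | Count | At withdrawal |
|---|---|---|---|
| Childhood Health Questionnaire | 0, 1, 2, 3, 6, 9, 12, 15, 18 | 9 | no |
| Childhood Health Assessment Questionnaire | 0, 1, 2, 3, 6, 9, 12, 15, 18 | 9 | no |
| Health Utilities Index Mark 2 | 0, 3, 6, 9, 12, 18, 27, 36 | 8 + withdrawal = 9 | yes |
| ACR paediatric core set | screening, 1, 2, 3, 6, 9, 12, 15, 18, 21, 24, 27, 30, 33, 36 | 15 + withdrawal = 16 | yes |

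**Data for end point 7.** Nine scheduled assessments: one baseline plus 9 − 1 = 8 later ones, covering the whole treatment period.

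**Age of the last value at exit.** After month 3, visits are 12 weeks apart with an allowance of 15 days. Someone who attended every visit and leaves just before the next one has a last questionnaire about 12 × 7 = 84 days old, or 84 + 15 = 99 days if the full allowance is used.

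**Number affected.** The Sample size section expects about 10% loss to follow-up among 154: 0.10 × 154 = 15.4, so about 15. This is an upper bound under that estimate, for two reasons:

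- it covers the whole trial, and losses after month 18 come after all nine questionnaires were due;
- it includes participants who simply stop attending and so have no withdrawal visit.

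The affected group is those who withdraw completely before month 18 and attend the visit. Its size is not given.

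**Effect on an arm mean.** If a fraction *f* of an arm withdraws, and stayers differ from leavers by *D*, the mean among stayers differs from the mean of the whole arm by *f* × *D*. The arm comparison is biased only if *f* × *D* differs between arms. The article gives neither *D* nor *f* by arm, so no size can be put on the bias.

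**Core set against questionnaire.** The core set is marked in 16 columns. It coincides with the Childhood Health Assessment Questionnaire in 8 (months 1, 2, 3, 6, 9, 12, 15, 18), leaving 16 − 8 = 8. One of these is screening, for which the month-0 questionnaire, at most 14 days later, can serve. The other 7 are months 21, 24, 27, 30, 33, 36 and premature withdrawal.

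**The case against.** Much of the case on the other side stands.

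- A reader might infer that end point 7 lacks data. It does not: it has a baseline and eight later assessments. With no time frame stated for the end point, ending at the end of treatment contradicts nothing. Health status by the Health Utilities Index, a separate end point, continues to months 27 and 36.
- A reader might infer that the analysis rests on complete cases alone. The Analysis plan also provides imputation sensitivity analyses informed by the reasons for missing data. Stopping treatment does not in itself end the questionnaires.
- Most leavers would have a questionnaire from the preceding visit, and an exit value does not of itself fill in a month-18 mean. This limits the gain. It does not remove it, because the exit value is what would inform those sensitivity analyses.
- A reader might infer that late ACR response cannot be derived. The documents do not show this. The core set has its own row to month 36 and at withdrawal, which on its face schedules all its variables. The article does not list the paediatric components. The phrase "disability index Health Assessment Questionnaire scores", under Known potential benefits, belongs to the adult criteria. The gap needs two unstated premises: that the childhood questionnaire is the functional item, and that it is collected only through its own row. Even then the core set would be incomplete, not absent.
- Taking the functional baseline at month 0 and the other core-set items at screening is of little weight, given the limit of 14 days between the two visits.

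The blank cells at premature withdrawal are not answered by any of this.

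**Conclusion.** The point holds in a limited form. Both instruments of end point 7 are missing from a withdrawal visit that takes place anyway and collects almost everything else, which sits badly with the stated aim of minimising missing data. It affects participants who withdraw completely before month 18 and attend that visit: an unstated number, at most about 15 of 154 on the article's loss estimate. It concerns a secondary end point, and no bias has been demonstrated. This reading assumes that the withdrawal column refers to leaving the study, not only to stopping treatment.

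The core-set issue is a request to reconcile two rows in seven columns. It is conditional on the assumption that the Childhood Health Assessment Questionnaire is the functional item of the core set and is collected only where its own row is marked. If the core-set row already includes it, one clarifying sentence is enough.

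**What to change.** 1. Mark both childhood questionnaires in the premature-withdrawal column of Table 1. The cost is a table amendment and a small added burden on families at an existing visit. At manuscript submission 58 of 154 participants had been recruited, so the change would cover the remaining 154 − 58 = 96 from entry, and those already enrolled who had not yet left.
2. State the time frame of end points 7 and 8. For end point 7, ending at month 18 can stay.
3. State whether the core-set row includes the Childhood Health Assessment Questionnaire. If the questionnaire is a core-set item not covered by that row, either collect it wherever the core set is marked, which adds it at six follow-up visits as well as at withdrawal, or limit end point 8 to month 18, which gives up ACR response during follow-up. In that case also name the month-0 questionnaire as the functional baseline.

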The risk of increased malignancy with azathioprine in patients with Crohn’s disease on infliximab is well-recognised [47,48]. As noted already, AEs associated with the recent adalimumab trial in JIA were associated with minimal safety signals [41]. A recent retrospective cohort study evaluated overall mortality and cancer mortality in relation to immunosuppressive drug exposure, including anti-TNF drugs, in adult patients with ocular inflammatory diseases [49]. The study did show an increased overall and cancer mortality in adult patients exposed to anti-TNF agents. The study’s authors acknowledge that these data need to be interpreted with caution because of the methodological issues associated with retrospective studies and the prevalence of comorbidity in patients taking anti-TNF drugs.

On the basis of adult patient data, as well as on the growing evidence base of published data derived from long-term follow-up in biologic registries, clinical trials and cohort studies, a number of important safety signals need to be considered in this trial. Patients taking TNF blockers are more susceptible to serious infections. Patients must therefore be monitored closely for infections, including TB, before, during and after treatment with adalimumab. Because the elimination of adalimumab may take up to 5 months, monitoring should be continued throughout this period.

AEs of the haematologic system, including medically significant cytopaenia (for example, thrombocytopaenia, leucopaenia) have been reported with adalimumab. All patients should be advised to seek immediate medical attention if they develop signs and symptoms suggestive of blood dyscrasias (for example, persistent fever, bruising, bleeding, pallor) while on adalimumab.

Adalimumab monotherapy, as well as concomitantly with MTX, has been studied in rheumatoid arthritis, polyarticular JIA and psoriatic arthritis patients [41]. Antibody formation to adalimumab itself was lower when adalimumab was given together with MTX compared to adalimumab monotherapy. Administration of adalimumab without MTX resulted in increased formation of antibodies, increased clearance and reduced efficacy of adalimumab. In patients with polyarticular JIA, adalimumab antibodies were identified in 27 (15.8%) of 171 patients treated with adalimumab. In patients not given concomitant MTX, the incidence of adalimumab antibodies was 22 (25.6%) of 86, compared to 5 (5.9%) of 85 when adalimumab was used as an add-on to MTX.

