### Analysis plan

The primary analysis will be carried out according to the principle of intention to treat all randomised participants as far as is practically possible. If consent to treatment is withdrawn but the participant agrees to remain in the study for follow-up, the participant will be followed until completion. If the participant decides to withdraw consent completely, however, the reasons for withdrawal of consent will be recorded (if possible) and reported for both groups.

The primary outcome is ‘time to failure’. Analysis of time to treatment failure will be summarised by Kaplan-Meier curves for each treatment group and compared overall using the logrank test and survival regression methods. For secondary outcomes, continuous data will be reported as differences in means and binary data will be reported in terms of the relative risk, each with 95% confidence intervals. Missing data will be monitored and strategies developed to minimise their occurrence. Missing data will be handled by considering the robustness of the complete case analysis in relation to sensitivity analysis using various imputation assumptions; however, these analyses will be informed by data collected on the reasons for missing data.

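### No sample for antibody to adalimumab is scheduled at premature withdrawal, permanent stop or failure, so the antibody incidence may be understated by an unknown amount

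*Protocol article*

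**What the plan says.** Secondary end points, item 4c, lists this outcome under safety, tolerability and compliance: "Development of human antihuman antibody to adalimumab determined with samples collected at 1, 6 and 18 months".

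Table 1 (Study visits and assessments) has 17 columns after the row label, the last headed "Premature withdrawal". The row "Samples for HAHA analyses" has a mark at screening and at month 3 and nowhere else. Haematology and biochemistry are both marked in the withdrawal column. The row's footnote allows one extra occasion: "To be done also as required if anaphylaxis occurs during trial". The table has no failure visit and no sample triggered by failure or by stopping study drug.

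The section Potential risks says why antibodies matter: "Administration of adalimumab without MTX resulted in increased formation of antibodies, increased clearance and reduced efficacy of adalimumab". It gives antibody rates from polyarticular JIA of 5/85 with MTX and 22/86 without.

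The Analysis plan bears on who remains available for sampling: "If consent to treatment is withdrawn but the participant agrees to remain in the study for follow-up, the participant will be followed until completion". For missing data it plans a complete-case analysis with "sensitivity analysis using various imputation assumptions".

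**The concern.** Antibody status is observed only at fixed visits, while the events that may go with antibodies (loss of effect, stopping, leaving) fall between them. If antibody-positive participants are over-represented among those who stop or leave early, the missing results depend on the quantity being estimated, and the observed incidence is too low.

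The outcome is a named safety end point of a trial whose background calls safety a major priority. Analysis cannot recover a sample that was never drawn. Imputation can show how far the answer might move, but not what a participant's status was on stopping.

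**Working it through.** **1. The two schedules against the events.**

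| | Table 1 | End-point text, item 4c |
|---|---|---|
| Antibody samples | screening, month 3 | months 1, 6, 18 |
| No post-baseline sample at all | those who leave before month 3 | those who leave before month 1 |
| Stops just after month 6, stays in study | no later sample | next sample at month 18, 12 months on |
| Leaves the study just after month 6 | no later sample | no later sample |
| Sample at withdrawal, stop or failure | none (anaphylaxis only) | none stated |

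The two schedules share no sampling time. Under Table 1 the last 18 − 3 = 15 months of treatment have no antibody sample. The gap at stopping or leaving exists under both schedules; only the number of participants affected differs.

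**2. When failure can occur (Primary end point; visit-interval rule under Table 1).** Worsening of existing comorbidity counts after 3 months, and persistence at an entry grade of 1 or 2 after 6 months. The medication and suspension criteria are introduced as applying after at least 3 months of therapy, although the medication item also says at any time. Readings that define failure must be at least 4 weeks apart. Many failures would therefore come after one post-baseline sample, but under Table 1 none after month 3 would be followed by another.

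**3. Figures given.** The cited rates reproduce: 5/85 = 5.9% with MTX and 22/86 = 25.6% without. Expected loss to follow-up is about 10%, and 102 are allocated to adalimumab, so 0.10 × 102 ≈ 10 participants. The article gives no figure for the bias.

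**4. Possible size (assumption range).** Let m be the share with no usable sample, p the rate in those sampled and q the rate in those not sampled.

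True rate = (1 − m) × p + m × q; understatement = m × (q − p).

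Take m = 0.10 and p = 5.9%:

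- q = 5.9% (same rate): true rate 5.9%, understatement 0.
- q = 25.6% (cited rate without MTX): 0.9 × 5.9 + 0.1 × 25.6 = 7.9%, understatement 2.0 points.
- q = 100% (extreme limit): 0.9 × 5.9 + 0.1 × 100 = 15.3%, understatement 9.4 points.

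Taking m as the full expected loss is itself an assumption, since some of those lost would already have given a sample. The formula also leaves out participants who have an early negative sample and convert later; they would count as negative. The article gives no rate for them, so no figure is attached.

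**The case against.** The strongest reply is that failure is an end-point event and not an exit. Treatment is planned for 18 months with follow-up to 3 years, and those who stop treatment but agree to stay are followed on. Only full withdrawal, within the expected loss of about 10%, removes later scheduled samples, and earlier ones remain. This stands, and it limits the number lost altogether. It does not supply status at the time of stopping: under Table 1 there is no sample after month 3, and under the end-point text the next may come a year later.

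A reader might infer a two- to three-fold understatement. That needs three things: only a month-18 sample counts, every failure goes unsampled, and antibody-positive participants fail at 60–80%. The article supports none of them. Its end-point text lists earlier samples, failures may stay under observation, and it gives no failure rate by antibody status.

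The efficacy link is stated for adalimumab without MTX, whereas everyone here continues MTX. This also stands, so the direction of bias is plausible but not shown.

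A reader might extend the point to the row "ANA, dsDNA and ENA", which is also blank at withdrawal. These autoantibodies do not measure immunogenicity to adalimumab, and no listed end point uses them, so the argument does not carry over. A further month-18 autoantibody draw would be a preference.

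Finally, this is a condensed article, and the full protocol may hold event-driven sampling. That is possible. But the article prints the schedule row by row, with a withdrawal column and a footnoted exception for anaphylaxis, and the sample is absent from both. The planned sensitivity analyses help to express the uncertainty but do not remove it.

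**Conclusion.** The point holds in a limited form. For a named secondary end point, no antibody sample is scheduled at premature withdrawal, permanent stop or declared failure, under either printed schedule. Participants who stop or leave between fixed samples have no antibody status at that point. Understatement is likely if antibodies reduce efficacy in patients who also take MTX, which the article does not establish.

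The size is unknown. On the assumptions of 5.9% observed and about 10% unsampled, it runs from nil to about 2 points at the cited rate without MTX; anything much larger needs a more extreme rate in the unsampled. The primary analysis is not affected. The change is worth making because it is cheap and the data cannot be recovered later.

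**What to change.** The antibody sampling times in Secondary end points, item 4c, and in Table 1 must be reconciled. In the same revision:

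- mark the antibody sample in the premature withdrawal column of Table 1;
- add an antibody sample at the visit where study drug is permanently stopped or treatment failure is declared;
- state that a participant counts as antibody-positive if any post-baseline sample, including these, is positive.

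The cost is one extra tube and one assay for each of those participants, with slightly more blood taken. Blood is already drawn at the withdrawal visit and at the scheduled treatment visits.
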